## Abstract

**Introduction:**

The Its Not JUST Idiopathic pulmonary fibrosis Study (INJUSTIS) is a multicentre, prospective, observational cohort study. The aims of this study are to identify genetic, serum and other biomarkers that may identify specific molecular mechanisms, reflecting disease endotypes that are shared among patients with progressive pulmonary fibrosis regardless of aetiology. Furthermore, it is anticipated that these biomarkers will help predict fibrotic activity that may identify patterns of disease behaviour with greater accuracy than current clinical phenotyping.

**Methods and analysis:**

200 participants with the multidisciplinary team confirmed fibrotic lung disease (50 each of rheumatoid-interstitial lung disease (ILD), asbestosis, chronic hypersensitivity pneumonitis and unclassifiable ILD) and 50 idiopathic pulmonary fibrosis participants, recruited as positive controls, will be followed up for 2 years. Participants will have blood samples, lung function tests, quality of life questionnaires and a subgroup will be offered bronchoscopy. Participants will also be given the option of undertaking blinded home handheld spirometry for the first 3 months of the study. The primary end point will be identification of a biomarker that predicts disease progression, defined as 10% relative change in forced vital capacity (FVC) or death at 12 months.

**Ethics and dissemination:**

The trial has received ethical approval from the National Research Ethics Committee Nottingham (18/EM/0139). All participants must provide written informed consent. The trial will be overseen by the INJUSTIS steering group that will include a patient representative, and an independent chairperson. The results from this study will be submitted for publication in peer-reviewed journals and disseminated at regional and national conferences.

**Trial registration number:**

NCT03670576.

## Introduction

Interstitial lung diseases (ILDs) are a group of immunoinflammatory and fibrotic diseases of the lung parenchyma. In a substantial number of patients there is progressive fibrosis of the alveoli and interstitium that leads to increasing disability and ultimately the death of patients with these diseases. Establishing the aetiology of these fibrotic lung diseases is often a clinical challenge and the relevance of aetiology to disease behaviour remains controversial. The best characterised fibrotic ILD is idiopathic pulmonary fibrosis (IPF), which has a median survival of 3 years, and 5-year survival of 25%, which is worse than most cancers.^1^ Other conditions characterised by progressive pulmonary fibrosis include asbestosis, chronic hypersensitivity pneumonitis (HP), rheumatoid arthritis-associated ILD (RA-ILD), where the aetiology is assumed, and unclassifiable ILD where the clinical phenotype does not precisely reflect IPF.^2^ The progression of these related conditions is also remorseless, and their genetic predisposition similar to IPF, raising the possibility of shared targetable mechanisms across disease phenotypes regardless of likely aetiology.

Recently two drugs, pirfenidone^3 4^ and nintedanib,^5^ have been approved for the treatment of IPF. While these drugs are described as ‘anti-fibrotic’, they can only be prescribed for IPF, rather than all forms of progressive fibrotic disease.^6^ Therefore, patients with pulmonary fibrosis where the aetiology has been assumed, or the clinical features aren’t specific for IPF, cannot receive antifibrotic therapy at the current time. However, the risk factors and molecular pathways driving fibrosis in aetiologically defined or phenotypically unusual pulmonary fibrosis may be similar to IPF, thus potentially resulting in a large number of patients not having access to life-prolonging therapy. Our understanding of IPF has improved significantly both in terms of biomarkers^7 8^ and clinical end points.^9^ However, there remains a significant gap in our understanding of non-IPF ILD, with currently no approved treatments or cure.

RA-ILD, seen in 5%–10% of patients with rheumatoid arthritis remains a significant life-limiting complication with mortality in excess of 10% compared with patients without ILD. Subclinical interstitial lung abnormalities (ILAs) are seen in 30%–50% but individual risk of progression to ILD is unknown.^10^ Chronic HP diagnosis rests on history of antigen exposure and radiological appearance, which often has an overlap with other ILDs. Sometimes, there is no known antigen exposure, and more recent hypotheses suggest a combination of exposure in genetically predisposed individuals.^11 12^ While acute HP has a good prognosis, chronic HP is a progressive disease lacking evidence-based treatments with current therapy relying on immunosuppression. Despite improvements in radiology and the advent of multidisciplinary teams (MDTs), unclassifiable ILD remains a significant burden of ILD in clinical practice and represents between 10% and 38% of all ILDs.^13 14^ These patients present a diagnostic challenge and again no evidence-based treatments are available.

Recent studies have highlighted phenotypical and molecular similarities across a range of ILDs. For example, the minor allele frequency of the MUC5B promoter single-nucleotide polymorphism (SNP), widely associated with IPF,^15^ is found with increasing frequency in patients with chronic HP.^16^ Short telomeres have also been associated with RA-ILD^17^ and chronic HP, resulting in a prognosis similar to patients with IPF.^16^ Patients with RA-ILD and usual interstitial pneumonia pattern have radiological changes that are indistinguishable from IPF and the presence of traction change and honeycombing is associated with poor outcomes regardless of aetiology.

Together, these features suggest that there may be shared mechanisms in the progression of pulmonary fibrosis common among patients with lung fibrosis due to a number of aetiologies. To explore this hypothesis, the Its Not JUST Idiopathic pulmonary fibrosis Study (INJUSTIS) will recruit a clinical cohort comprising of ILD subgroups, to explore genetic, serum and clinical biomarkers that may distinguish progressive fibrosing lung disease phenotypes regardless of aetiology. This may then eventually enable therapeutics targeting specific mechanisms of disease rather than clinical phenotypes of disease.

## Methods and analysis

### Objectives

INJUSTIS is a prospective multicentre observational cohort study that will be managed through the Nottingham Respiratory Research Unit and funded by the National Institute of Health Research (NIHR) through the Nottingham Biomedical Research Centre and an NIHR professorship ([name]).

The primary objective is to:

Identify biomarkers that determine progressive fibrotic lung disease irrespective of aetiology.

The secondary objectives are to:

Identify biomarkers that predict all-cause mortality.Identify biomarkers that predict changes in QoL scores.Identify biomarkers that predict the development of disease complications (respiratory failure and acute exacerbations).Investigate genetic association and epigenetic modifications which affect fibrotic disease severity and progression.Prospectively evaluate longitudinal disease behaviour in patients with non-IPF fibrotic lung diseases with a view to developing composite clinical end points for subsequent use in intervention studies.Explore association of environmental exposures with disease progression and all-cause mortality.Investigate whether home handheld spirometry over 3 months predicts disease progression and survival.

The primary end point will be:

Disease progression defined as relative forced vital capacity decline ≥10% or death within 12 months.

Secondary end points are:

All-cause mortality at time of censoring.Number of acute exacerbations over 2 years.Change in Quality of Life (QoL) Questionnaire Scores from baseline to 12 weeks.Rate of change in biomarker activity from baseline to 12 weeks.Change in diffusing capacity of the lung for carbon monoxide (DLco) from baseline to 12 months.Change in 6 min walk distance from baseline to 12 months.Change in transcriptomic profiles from baseline to 12 weeks.Change in home handheld spirometry values from baseline to 12 weeks.

### Selection of participants

Two hundred participants with recently diagnosed (within 18 months of study start date) fibrotic lung disease (50 each of rheumatoid-ILD, asbestosis, chronic HP and unclassifiable ILD) and 50 IPF participants as positive controls will be recruited from ILD clinics locally and across the UK. Only participants with MDT confirmed diagnosis of fibrotic ILD with radiological evidence of parenchymal lung fibrosis evidenced by reticulation and traction bronchiectasis, with or without honeycomb change will be recruited. Those with inflammatory radiological changes without evidence of fibrosis will not be deemed suitable regardless of clinical phenotype.

Recruitment will be reviewed on an ongoing basis and should rates fall below the expected levels, additional National Health Service (NHS) sites within the UK will be considered for participation. Eligible patients who meet the inclusion/exclusion criteria will be invited to consent. Most participants will be identified through outpatient clinics, but recruitment will not be restricted to this route. It will be explained to participants that entry into the study is entirely voluntary and that further treatment and care will not be affected by a decision to not partake. It will be clearly stated that participants are free to withdraw from the trial at any time. All participants will provide written informed consent, which will be countersigned by a member of the study team.

Inclusion criteria:

Male or female aged ≥18 years.Able and willing to give written informed consent.Recently diagnosed (defined as diagnostic CT scan or surgical lung biopsy (if applicable) within 18 months of study start date).An MDT diagnosis of fibrotic ILD defined as the presence of traction change and reticulation with or without honeycombing within the lung parenchyma associated with either:Rheumatoid arthritis (rheumatologist diagnosed with anti-cyclic citrullinated peptide antibodies and/or rheumatoid factor positive).Asbestosis (appropriate occupational history and radiological evidence of asbestos exposure).Chronic HP in accordance with consensus criteria^11^ (appropriate exposure history, radiological features ± avian and fungal precipitins).Unclassifiable fibrotic lung disease (fibrotic lung disease otherwise unclassifiable despite extensive clinical and radiological examination).IPF in accordance with consensus criteria (American Thoracic Society (ATS), European Respiratory Society (ERS), Japanese Respiratory Society (JRS, Latin American Thoracic Society (ALAT) guidelines).^18 19^

Exclusion criteria:

Participating in an interventional clinic trial.Asymptomatic ILAs and normal lung function.Change in clinical phenotype from initial radiological diagnosis to screening.Any connective tissue disease other than rheumatoid arthritis.Acute HP.Participants who do not possess a smartphone cannot partake in the domiciliary spirometry.

#### Study regimen

Both cases and IPF controls will undertake the same investigations. Following informed consent, the following test results, previously carried out as part of the participant’s usual NHS care, will be used for the purposes of the study:

HRCT findings.Blood results.Lung function tests.Bronchoscopy samples if already taken.

All participants will have baseline investigations at the first visit having provided informed consent. At the first visit, 40 mL of blood will be obtained, full lung function tests and a 6 min walk test will be performed. Participants will also be asked to complete QoL Questionnaires (Medical Research Council Dyspnoea Scale,^20^ Leicester Cough Questionnaire,^21^ IPF-abridged Profile for Assessment and Referral to Care,^22^ King’s Brief ILD Questionnaire^23^ and EQ-5D-5L).^24^ If consent is given for optional bronchoscopy, this will be subsequently performed and bronchoalveolar lavage carried out. Participants with a smartphone will be given the option of a home handheld spirometer and asked to provide daily FVC readings for the first 3 months of the study period.

Further visits at 3 months, 12 months and 24 months will include further 40 mL blood sampling, QoL and full lung function analysis. At 12 months and 24 months a 6 min walk test will be repeated (figure 1).

**Figure 1 F1:**
[figure not shown]
Legend – participant flow through the study.

The majority of initial sample processing will be performed at the participant’s local NHS hospital trust via the Clinical Research Network. Participation in the study will be for 2 years. Other than initial assessment and follow-up visits at 3 months, 12 months and 24 months, there will be no further assessments. Only participants recruited at Nottingham University Hospitals NHS Trust will be offered a study bronchoscopy. It is not anticipated that any data will be obtained before completion of study that would lead to discontinuation of the study. For individual participants, discontinuation will be decided on an individual basis. The end of study will be defined as the last patient to complete the 2 years of follow-up.

### Specimen processing and analysis

All human tissue (blood, lavage, biopsy, etc.) samples will be processed and stored in accordance with the Human Tissue Act (2004). All biological samples will be processed within 2 hours of being obtained according to local standard operating procedures and stored in 500 µl aliquots at −80°C until analysis. Sample analysis will take place either at the University of Nottingham or in the laboratories of third party national, or international, academic partners or contract research organisations following appropriate tissue transfer agreements.

The primary analysis will include measurement of epithelial biomarkers [matrix metalloproteinase-7 (MMP-7), cancer antigen 125 (CA-125), carbohydrate antigen 19-9 (CA19-9), surfactant protein D (SP-D)]) and markers of matrix turnover [C-reactive protein degraded by MMP-1/8 (CRPM), collagen 3 degraded by MMP-9 (C3M) and collagen 6 degraded by MMP-2/9 (C6M)) as well as genotyping for mucin 5B (*MUC5B)*, desmoplakin (*DSP)* and A-kinase anchoring protein 13 (*AKAP13)*. Exploratory analysis will include whole genome sequencing, RNA sequencing, proteomic and metabolomic analysis to identify novel biomarkers that predict fibrotic disease behaviour. Biopsy material will be used to culture cellular components, frozen for extraction of protein, RNA and DNA or formalin-fixed paraffin embedded.

Any additional samples will be archived for future genetic and biomarker studies in the University of Nottingham premises at the Nottingham City Hospital. The Human Tissues Authority license number is 12 265. Where participants do not agree to the future use of the samples they will be destroyed in accordance with the Human Tissue Act, 2004.

#### Details of spirometry

A secondary objective of this study is to determine whether change in daily home (domiciliary) handheld spirometry values over 3 months can predict disease progression and overall survival.

Participants wishing to take part in home spirometry will be provided with a portable handheld spirometer (MIR Spirobank Smart) linked to an electronic health journal (patientMpower smartphone application) on enrolment. Participants will be trained to undertake daily spirometry readings (one forced expiratory manoeuvre/day; seated) for the first 3 months of the study period. All spirometry readings will be blinded to participants and automatically uploaded to patientMpower via the smartphone application, ensuring full encryption throughout. Participants will therefore need to possess, and be confident in using, a smartphone device and have an email address. The spirometry data will then be transferred to the University of Nottingham for further analysis. Participants will be able to continue to use the spirometer and patientMpower application with open display of FVC readings after the initial 3-month observation period if they wish.

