#### Statistics

The primary end point of disease progression (10% relative FVC decline or death within 12 months) will be used dichotomously across all subgroups collectively analysed together, with the exception of IPF controls. Association of baseline biomarker levels with dichotomous disease progression and overall survival will be analysed using binomial family of generalised linear models, while Gaussian family or otherwise appropriate models will be used to assess associations with continuous secondary end points. The Benjamini-Hochberg procedure will be applied to account for multiplicity as appropriate. Repeated measures mixed models will be used to assess associations over time, which includes time points within one model and circumvents correction for multiple testing. Fixed factors will include baseline demographic information. Where putative biomarkers are identified, end point data will be used to compare biomarker levels by time-to-event through proportional hazard models; comparable ability to predict end points will be assessed through sensitivity and specificity analyses (receiver operator characteristic curves).

To identify transcriptomic biomarkers, RNA-seq libraries will be prepared and entered into a workflow for read count normalisation enabling quantification of transcript expression; normalisation ensures length and abundance of cDNA reads are corrected according to other genes (reads per kilobase per million) and further library scaling can occur.^25 26^ Libraries, aligned to an appropriate reference genome, will enable detection of differential gene expression and SNPs/variants according to primary end point and secondary measures of disease severity. Transcript-discovery artefacts, transcripts that remain below detectable levels of change across compared samples, as well as any with zero mapped reads will be excluded. R statistical packages will be used for these bioinformatics workflows.

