Further statistical analyses will be performed to determine associations between identified biomarkers and exploratory secondary objectives. Statistical approaches include, but are not limited to, correlation and analyses of variance between biomarker levels and patient-reported QoL outcomes or disease exacerbations; machine learning strategies on home spirometry to detect decline in lung function, and subsequent comparison of sensitivity with traditional spirometry measures at predicting end points. Factor analysis approaches will be used to reduce dimensions of data sets and assess clustering; generalised linear models will be used to test associations.

Confounding factors are particularly important in studies that hope to offer causal inference of biomarkers on clinical outcomes,^27^ and corrections to adjust for these will be applied in the analysis as proposed by the directed acyclic graph (figure 2).^28^ Fixed factors in mixed models will include baseline demographic information: age, gender, body mass index and smoking status. Exposure history in patients with chronic HP will be collected as will time from diagnosis to enrolment across all subgroups and adjusted for as a potential confounder. Some participants may be on background therapies such as immunosuppression and corticosteroids. While these therapies are likely to be confounders, it is possible they may decrease or increase progression of fibrosis based on the PANTHER (Prednisone, Azathioprine, and *N*-Acetylcysteine: A Study That Evaluates Response in Idiopathic Pulmonary Fibrosis) Study.^29^ Therefore, models will include treatment strategy as part of the minimal set of adjustment for estimating direct effect on end point. The objectives of the study do not extend to assessing treatment effect. Further unknown confounders will be identified from the spirometry smartphone application that will collect various data such as air quality index to inform limitations and future study.

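### Home FVC change over months 0–3 is tested as a predictor of progression over months 0–12, so the first-quarter FVC loss is counted in both

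*Protocol article*

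**What the plan says.** All references are to the Protocol article.

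- **Predictor.** Participants who opt for home spirometry are "asked to provide daily FVC readings for the first 3 months of the study period" (Study regimen). The matching secondary end point is "Change in home handheld spirometry values from baseline to 12 weeks" (Objectives). The aim is to "determine whether change in daily home (domiciliary) handheld spirometry values over 3 months can predict disease progression and overall survival" (Details of spirometry).
- **Outcome.** Progression is defined once: "Disease progression defined as relative forced vital capacity decline ≥10% or death within 12 months" (Objectives). The Statistics section repeats it, and no other definition is given for the home spirometry objective.
- **Clinic FVC.** "Further visits at 3 months, 12 months and 24 months will include further 40 mL blood sampling, QoL and full lung function analysis" (Study regimen). The text under Figure 1 adds: "Other than initial assessment and follow-up visits at 3 months, 12 months and 24 months, there will be no further assessments".
- **Comparison.** Statistics plans machine learning on the home readings and "subsequent comparison of sensitivity with traditional spirometry measures at predicting end points".
- **Main biomarker analysis.** "Association of baseline biomarker levels with dichotomous disease progression and overall survival will be analysed using binomial family of generalised linear models" (Statistics).

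**The concern.** A predictor should be known before the outcome it predicts begins to accrue. Here the predictor is FVC change in the first quarter and the outcome is FVC change (or death) over the whole year, so one is a component of the other. They correlate even if the first quarter carries no information about the following nine months. The study could then report that three months of home spirometry predicts progression when it has partly measured that progression.

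The home-versus-clinic comparison adds a second problem. Home and clinic FVC come from different devices, so home change shares only true FVC loss with the end point. A 3-month clinic change would also share the baseline clinic reading, including its error. Neither method need have forward value for clinic to look better.

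**Working it through.** The plan gives no AUC, power or sample size for this objective, so there is no figure of its own to reproduce. The check asks what the planned analysis would show if 3-month change had no forward value.

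**From the document.** Predictor window months 0–3; outcome window months 0–12; threshold 10%; clinic FVC at 0, 3, 12 and 24 months; 50% progression (Sample size justification).

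**Assumed, because the document gives no FVC variances.** True relative FVC change has independent increments with variance proportional to time. The 12-month SD is 10 points, so the variance is 100: 25 in months 0–3 and 75 in months 3–12. Clinic error has SD *c* per visit (0, or 3–5). Error in the home change has SD *h* (0, or 3–6). Deaths are ignored.

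**Step 1: correlations with the baseline-to-12-month change.**
- Home: r = 25 / √[(25 + h²)(100 + 2c²)]
- Clinic 3-month change: r = (25 + c²) / √[(25 + 2c²)(100 + 2c²)]

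**Step 2: AUC at 50% progression.** For jointly normal variables split at the median, AUC = ½ + (2/π)·arcsin(r/√2).

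| c | h | Home r | Home AUC | Clinic r | Clinic AUC |
|---|---|---|---|---|---|
| 0 | 0 | 25/√(25×100) = 0.50 | 0.73 | 0.50 | 0.73 |
| 3 | 3 | 25/√(34×118) = 0.395 | 0.68 | 34/√(43×118) = 0.477 | 0.72 |
| 5 | 6 | 25/√(61×150) = 0.261 | 0.62 | 50/√(75×150) = 0.471 | 0.72 |

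Simulation agrees. With error in both devices, home AUC is about 0.62–0.69 at 30–50% progression and reaches 0.70 at 20%. In the middle row, a 5% test of home change rejects in 58%, 89% and 99.7% of samples of 50, 100 and 200 home users. The document does not say how many users to expect.

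**Step 3: only clinic error, no true change.** Home AUC is 0.50. Clinic 3-month change has r = c²/(2c²) = 0.50 and AUC 0.73, entirely through the shared baseline reading.

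**Step 4: outcome counted from the 3-month clinic FVC.**
- Home: covariance 0, AUC 0.50. The simulated 5% test rejects in 4.8%, 4.9% and 5.5% of samples of 50, 100 and 200.
- Clinic 3-month change: the 3-month reading now ends the predictor and starts the outcome, so its error enters with opposite signs. r = −c² / √[(25 + 2c²)(75 + 2c²)]. For c = 3, −9/√(43×93) = −0.142, AUC 0.44. For c = 5, −25/√(75×125) = −0.258, AUC 0.38. With error only, r = −0.50 and AUC 0.27.

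A month-3 landmark therefore repairs the home analysis but reverses the bias for clinic change.

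**Step 5: 12-month FVC conditional on 3-month clinic FVC.** Let B be the between-person SD of baseline FVC. Given the 3-month reading, the residual covariance with 12-month FVC is 25c²/(B² + 25 + c²) for home change and −c²B²/(B² + 25 + c²) for clinic change. With an assumed B = 15 and c = 3 these are 225/259 = 0.9 and −2025/259 = −7.8; without conditioning, the clinic value is −9. The conditional model is nearly clean for home change but leaves most of the shared error in clinic change.

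**The case against.** **Early loss is part of progression, and detecting it early is useful.** True, and Statistics does speak of detecting decline. But the objective and the planned comparison are both worded as prediction, and an AUC of 0.73 with no forward value would be read as prognostic.

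**A landmark is analysis-plan detail.** A plan not shown may contain one. The point does not rest on that omission: the predictor window, the single outcome definition and the predictive aim are all stated here, and together they overlap.

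**Counting from baseline is inferred.** The definition does not name a starting point. With clinic visits only at 0, 3, 12 and 24 months, a 12-month decline has no other natural origin.

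**The clinic comparator is inferred.** This stands. Statistics says only traditional spirometry measures. Baseline clinic FVC would also fit those words, and the bias described for clinic 3-month change applies only if that change is the comparator.

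**The size is assumed.** This stands too. An AUC of 0.73 needs error-free home readings, and the plan has one manoeuvre per day at home, so the range with error is the more realistic one.

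**Weight.** Home spirometry is optional and serves one of seven secondary objectives.

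**Conclusion.** The concern holds for home FVC change over months 0–3 against progression over months 0–12. Under independent increments with a 12-month SD of 10 points, a home predictor with no forward value gives an AUC of about 0.73 without error, and about 0.62–0.69 with home-change error SD 3–6 and clinic error SD 3–5. The exact values depend on these assumptions; the direction does not. The home-versus-clinic comparison favours clinic if the comparator is the 3-month clinic change.

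A reader might infer more than the document supports:
- *That every 3-month predictor is affected alike.* A serum marker is not a component of FVC change. Its overlap is in time only and misleads only if the marker moves with concurrent FVC loss.
- *That the survival analysis is affected alike.* Overall survival has no FVC component. What remains is that a complete 3-month change requires survival to about month 3.
- *That the primary analysis is compromised.* It uses baseline biomarker levels and is untouched.

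This should be corrected, but it does not threaten the study's main result.

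**What to change.** 1. **Home change.** Assess it from a month-3 landmark: participants alive at the 3-month visit; progression as a relative decline of at least 10% from the 3-month clinic FVC to 12 months, or death in months 3–12; survival time counted from month 3.
2. **Home versus clinic.** Name the clinic comparator. If it is the 3-month clinic change, do not let the same 3-month reading end that predictor and start the outcome. One option is to model 12-month FVC conditional on 3-month clinic FVC and ask what home change adds. The clinic-change coefficient in that model still carries shared error, so report that remaining bias. Deaths after month 3 share no FVC reading with either predictor and can serve as a supporting comparison, though events may be few.
3. **Wording.** Describe any analysis against the baseline-to-12-month end point as early detection, not prediction.

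The cost is analysis wording only, since the 3-month clinic FVC is already collected. The downside is that events in the first 3 months are not used. In the simulations, about 3–17% of progressors had already truly fallen by 10 points at month 3.
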